**11 Blinding**

This trial employs oxiracetam and a placebo as controls and adopts a double-blind design. Placebo medications for L-oxiracetam and oxiracetam were prepared by the sponsor to achieve blinding. Simulated agents are uniformly packaged, ensuring that drug categories cannot be distinguished by appearance and meeting preparation requirements.

Additionally, each clinical trial unit designated specific research nurses for drug dispensing and administration, ensuring they did not disclose drug allocation to participants, were not involved in trial assessments, and were solely responsible for drug preparation and administration. Unblinding procedures could be initiated through the IWRS in case of SAEs, deterioration, or disease progression in participants.

The double-blind design involves a first-level blinding, where the blind codes correspond to the treatment groups (L-oxiracetam, oxiracetam, or placebo) assigned to each case number. The randomization code list was created by the statistical unit, and the blind codes were individually sealed in duplicate, stored separately at the leading unit and the sponsor's site.

**12 Randomization**

In this trial, a block randomization method will be used with a ratio of 2:2:1, where successfully screened subjects will be randomly assigned to three groups. The study employs a centralized randomization procedure, with each center competing for participant enrollment. The Department of Biostatistics at the School of Public Health, Nanjing Medical University, provide the centralized randomization system. Following the confirmation of each eligible subject by the center's investigator, researchers at each center will log into the system, input screening data, obtain a random number and drug code, and dispense the investigational drug accordingly.

**13 Statistical Analysis of Datasets: Definition and Selection**

Full Analysis Set (FAS): The FAS operates under the Intention-To-Treat (ITT) principle, analyzing all cases that have been randomized into groups and have used the medication at least once. For cases where the entire course of treatment is not observable, the last observed data are carried forward to the final outcomes of the trial. According to the ITT principle, all patients are analyzed according to the groups into which they were randomized. This approach aims to maintain the benefits of randomization and to avoid biases that might arise from excluding patients who did not complete the treatment as originally planned.

PPS: The PPS consists of a subset of the FAS, generated from cases that have adhered closely to the trial protocol. This set includes all participants who completed the prescribed treatment and follow-up without any serious violations of the trial protocol. The precise definition of what constitutes a serious violation will be finalized during the data review process.

Safety Analysis Set (SS): The SS is used for the evaluation of safety and tolerability. It includes all participants who, after randomization, received at least one treatment and underwent at least one safety evaluation. In safety analyses, patients are analyzed based on the actual medication group they received, which helps in assessing the safety profile of the drug across different patient groups and treatment conditions. This dataset is crucial for identifying any potential adverse effects associated with the treatment.

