| **Statistical Analyses:**  SAS 9.4 was used for data analysis independently conducted by a biostatistician unaware of the allocation. Continuous variables will be presented as mean ± standard deviation (SD) with a 95% confidence interval (CI) for normal distribution and as median (range) for abnormal distribution. Categorical variables will be expressed by numbers and percentages.  All hypothesis tests were two-sided with α = 0.05. A P-value ≤ 0.05 indicated statistical significance. Analysis followed the intention to treat (ITT) principle, including all randomized cases receiving at least one drug dose. For cases with incomplete treatment process, the last observed data were carried forward to the trial's final results.  When comparing the change values from baseline for each group, an analysis of covariance (ANCOVA) model was used, adjusting for baseline, injury classification, and education level. |
| **Target Sample Size:**  Before conducting this study, we conducted a pilot trial: The change values of the total scores on the LOTCA scale at 90 days post-drug cessation compared to baseline for L-oxiracetam and oxiracetam were 26.0 ± 11.8 and 22.8 ± 10.0, respectively. The combined SD for both groups was 11.0, with α set at 0.05 and 1-β at 0.8. Employing an optimal design with a sample ratio of 1:1, PASS software calculated a sample size of 190 cases for each group.  The change values of the total scores on the LOTCA scale at 90 days post-drug cessation compared to baseline for the L-oxiracetam group and the placebo group were 26.0 ± 11.8 and 20.0 ± 11.4, respectively. The combined SD for both groups was 11.6, with α set at 0.05 and 1-β at 0.8. Employing an optimal design with a sample ratio of 2:1, PASS software calculated a sample size of 204 cases for the L-oxiracetam group and 102 cases for the placebo group.  Considering potential dropouts, we increased the sample size by 15%. Therefore, the sample sizes for the L-oxiracetam group, oxiracetam group, and placebo group were set at 236, 236, and 118, respectively. |
| **Trial Period:**  September 2019- May 2024. |

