**7 Endpoints evaluation criteria**

**7.1 Efficacy** **Endpoints:**

7.1.1 Primary endpoint

- The primary outcome measure is the change in scores on the LOTCA at 90 days post-treatment compared to baseline.

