**10 Sample size calculation**

Before conducting this study, we conducted a pilot trial: The change values of the total scores on the LOTCA scale at 90 days post-drug cessation compared to baseline for L-oxiracetam and oxiracetam were 26.0 ± 11.8 and 22.8 ± 10.0, respectively. The combined standard deviation (SD) for both groups was 11.0, with α set at 0.05 and 1-β at 0.8. Employing an optimal design with a sample ratio of 1:1, PASS software calculated a sample size of 190 cases for each group.

The change values of the total scores on the LOTCA scale at 90 days post-drug cessation compared to baseline for the L-oxiracetam group and the placebo group were 26.0 ± 11.8 and 20.0 ± 11.4, respectively. The combined SD for both groups was 11.6, with α set at 0.05 and 1-β at 0.8. Employing an optimal design with a sample ratio of 2:1, PASS software calculated a sample size of 204 cases for the L-oxiracetam group and 102 cases for the placebo group.

Considering potential dropouts, we increased the sample size by 15%. Therefore, the sample sizes for the L-oxiracetam group, oxiracetam group, and placebo group were set at 236, 236, and 118, respectively.

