**14 Statistical analysis plan**

SAS 9.4 was used for data analysis independently conducted by a biostatistician unaware of the allocation. Continuous variables will be presented as mean ± SD with a 95% CI for normal distribution and as median (range) for abnormal distribution. Categorical variables will be expressed by numbers and percentages. All hypothesis tests were two-sided with α = 0.05. A P-value ≤ 0.05 indicated statistical significance.

The analysis for the primary outcome was conducted using analysis of covariance (ANCOVA). The least squares means of change from baseline at 3 months in LOTCA scores, as well as the mean differences between groups (L-oxiracetam vs. oxiracetam/ Placebo) and 95% CIs were estimated. Cohen’s d and 95% CI was used to calculate the effect size. For the secondary continuous efficacy outcomes, mean differences with corresponding 95% CIs were also analyzed using ANCOVA. For categorical outcomes of GOS-E, the rate differences and 95% CIs between groups were estimated using the approximate normality method and statistically tested with Fisher's exact probability test. All models were adjusted for age, sex, education, and TBI severity at baseline. Stratified analyses were performed to explore the efficacy of the L-oxiracetam intervention on cognitive function in patients with different age (< 60 vs. 60 + years), sex (male vs. female), education (none vs. Primary vs. Secondary school or Higher), and TBI severity (mild vs. moderate). Moreover, multiplicative interactions were tested by including a cross-product item in the model for the intervention group with age, sex, education, or TBI severity.

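### LOCF is the only missing-data rule stated for the full analysis set, in patients expected to gain 20 to 26 LOTCA points by Day 90; it freezes recovery in dropouts, can bias the contrast either way, and can cost power against oxiracetam

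*Protocol*

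**What the plan says.** Section 7.1.1 fixes the endpoint: "The primary outcome measure is the change in scores on the LOTCA at 90 days post-treatment compared to baseline". Section 14 gives the analysis: "The analysis for the primary outcome was conducted using analysis of covariance (ANCOVA)", with two-sided tests at 0.05.

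Missing data are covered by one rule, stated twice. Section 13, under the full analysis set (every randomised patient with at least one dose), says that where the treatment course cannot be fully observed, "the last observed data are carried forward to the final outcomes of the trial". The Synopsis says: "For cases with incomplete treatment process, the last observed data were carried forward to the trial's final results". The protocol names no alternative method and no sensitivity analysis for this rule.

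The Trial Schedule and Sections 5.11 to 5.13 place LOTCA at screening, at the end of the 14-day treatment period and at Day 90. The Day 30 and Day 60 contacts are telephone calls for the Barthel Index only. Section 4.3.3 asks sites to try to obtain a last assessment from patients who leave early.

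On size, Section 10 says: "Considering potential dropouts, we increased the sample size by 15%". The final numbers are 236, 236 and 118.

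**The concern.** LOCF gives a fair Day 90 value only if the score would not have moved after the last visit. Here the protocol's own planning figures say that it moves a great deal. Phase II gains by three months were 26.0 points on 4 g/day, 22.8 on oxiracetam and 20.0 on placebo (Section 1.3.4.3). Recovery is steep in every arm, so the carried value errs in a known direction.

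With three scheduled LOTCA assessments there are few values to carry. A patient who leaves before the end-of-treatment test has baseline as the last value and is scored as zero change, unless the last assessment sought in Section 4.3.3 is obtained. If the rule also covers patients who finish treatment but miss Day 90, they stay at the end-of-treatment score.

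The arms then differ at Day 90 partly because of how many patients left and when. Sections 4.3.1 and 4.3.2 list adverse events, poor compliance and perceived lack of effect among the reasons for leaving, so equal dropout across arms cannot be taken for granted. At stake are the type I error of the primary test and the power of the smaller of the two planned contrasts.

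**Working it through.** **Inputs.** From Section 10: means 26.0 and 22.8 (difference 3.2) with SD 11.0 against oxiracetam; 26.0 and 20.0 (difference 6.0) with SD 11.6 against placebo; 236, 236 and 118 patients. From Section 14: two-sided α of 0.05. Assumed, because the protocol does not give them: the dropout proportion d and its timing by arm, and the share f of the Day 90 gain already present in the carried score.

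**The plan's own figure.** n per group = 2 × 11.0² × (1.960 + 0.842)² / 3.2² = 185.5, so 186 (187 with the t distribution). The protocol's 190 is close, and power at 190 is 0.81. With 236 per arm and nothing missing, power is 0.885. On 85% of 236 observed (about 200 per arm), without carried values, it is 0.83.

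**Model for LOCF.** A share 1 − d has the planned Day 90 mean m and SD s. Of the dropouts, a share q carries baseline (change 0) and the rest carry f·m, with SD s_c equal to either f·s or the full 11.0.

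- mean = m × [(1 − d) + d(1 − q)f]
- variance = (1 − d)(s² + m²) + d(1 − q)(s_c² + f²m²) − mean²
- power = Φ(difference / SE − 1.96)

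**Equal 15% dropout, baseline carried for all.**
- L-oxiracetam: mean 0.85 × 26.0 = 22.10; variance 0.85 × (121 + 676) − 22.10² = 189.0.
- Oxiracetam: mean 0.85 × 22.8 = 19.38; variance 0.85 × (121 + 519.8) − 19.38² = 169.1.
- Difference 2.72; SE = √[(189.0 + 169.1)/236] = 1.232; power = Φ(2.208 − 1.960) = 0.60.

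**Other timings, equal 15% dropout, L-oxiracetam versus oxiracetam.**

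| When dropouts leave | f | Difference | Power, s_c = 11.0 | Power, s_c = f·s |
|---|---|---|---|---|
| Half before the end-of-treatment test | 0.5 | 2.84 | 0.68 | 0.70 |
| Half before | 0.9 | 2.94 | 0.73 | 0.74 |
| All after | 0.5 | 2.96 | 0.78 | 0.82 |
| All after | 0.7 | 3.06 | 0.84 | 0.86 |

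When all leave after the end-of-treatment test, power crosses 0.80 at f of about 0.45 (s_c = f·s) or 0.57 (s_c = 11.0). If every dropout carries baseline, about 4.4% dropout is enough to bring power to 0.80.

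**Placebo contrast, equal 15% dropout.** Power is 0.92 if all carry baseline and 0.98 to 0.99 if all carry half the gain.

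**Unequal dropout, no true effect** (both means 22.8, SD 11.0, 236 per arm).
- 5% versus 10%, baseline carried: means 21.66 and 20.52; false difference 1.14 points, which is 36% of 3.2; SE 1.119; two-sided rejection 0.175.
- 5% versus 10%, half the gain carried: 0.57 points; SE 1.02; rejection 0.086 (0.084 with s_c = 11.0).
- 5% versus 10%, 70% of the gain carried: 0.34 points; rejection 0.063.

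The false difference favours the arm that loses fewer patients, whichever arm that is.

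**The case against.** Several points against the concern have force.

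- A reader might infer that LOCF takes power below 80% outright. The protocol does not support that. It gives no end-of-treatment LOTCA change and no dropout timing. Because 236 per arm starts at 0.885, power against oxiracetam stays above 0.80 if most dropouts leave late with well over half of the gain. The placebo contrast does not fall below 0.92 under equal 15% dropout.
- A reader might also infer that all dropouts enter with values near zero. That holds only for those who leave before the end-of-treatment test without a last assessment. Treatment lasts 14 days and is given daily by a nurse, so placing all 15% inside it is an outer bound. Section 4.3.3 mitigates early loss, though only as a best effort.
- The wording ties LOCF to an incomplete treatment course. Whether it reaches a patient who finishes treatment and misses Day 90 is unclear. That a patient who dies keeps the last live score is likewise an inference, as is the idea that Section 10 removes dropouts from the analysis; no section says either.
- Under equal dropout, the attenuation is conservative for a superiority claim. The 17% rejection rate belongs to one chosen scenario.
- Missing-data detail often sits in a statistical analysis plan that is not shown.

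The last point does not rescue the plan. The protocol does not leave the method open: it fixes LOCF, and a later plan that follows the protocol inherits it. The per-protocol set in Section 13 requires completed treatment and follow-up, so it is no substitute. The other points limit the size of the concern, and the verdict reflects them.

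**Conclusion.** The concern holds as a badly chosen rule, not as a proven loss of power. LOCF is the only stated method, and the planning gains of 20.0 to 26.0 points contradict its premise in every arm. Equal dropout attenuates the contrast; unequal dropout can create a false difference in either direction.

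For L-oxiracetam versus oxiracetam with an assumed equal 15% dropout, power is about 60% if all leave before the end-of-treatment test, 68% to 74% if half do, and 78% to 86% if all leave after it with 50% to 70% of the gain carried. These figures are normal approximations without covariate adjustment; ANCOVA could raise them somewhat.

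Confidence is high that the rule is unsuitable and low on which power figure would apply. This should be fixed before unblinding, but it does not by itself invalidate the design.

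**What to change.** In Section 13 and the Synopsis, replace LOCF as the primary method, and align Section 14, by one of two routes:

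- a likelihood-based repeated-measures model (MMRM or a constrained longitudinal model) on LOTCA at baseline, end of treatment and Day 90, with the Day 90 treatment contrast as the primary estimate; or
- multiple imputation followed by the stated ANCOVA.

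Keep LOCF as a sensitivity analysis and add a tipping-point analysis. State how deaths are handled in the analysis, and say which patients the missing-data rule covers, in particular those who complete treatment but miss Day 90.

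The cost is wording and programming; the LOTCA visits needed are already scheduled. The downside is that both routes rely on data being missing at random, which the tipping-point analysis probes.

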**14 Statistical analysis plan**

SAS 9.4 was used for data analysis independently conducted by a biostatistician unaware of the allocation. Continuous variables will be presented as mean ± SD with a 95% CI for normal distribution and as median (range) for abnormal distribution. Categorical variables will be expressed by numbers and percentages. All hypothesis tests were two-sided with α = 0.05. A P-value ≤ 0.05 indicated statistical significance.

The analysis for the primary outcome was conducted using analysis of covariance (ANCOVA). The least squares means of change from baseline at 3 months in LOTCA scores, as well as the mean differences between groups (L-oxiracetam vs. oxiracetam/ Placebo) and 95% CIs were estimated. Cohen’s d and 95% CI was used to calculate the effect size. For the secondary continuous efficacy outcomes, mean differences with corresponding 95% CIs were also analyzed using ANCOVA. For categorical outcomes of GOS-E, the rate differences and 95% CIs between groups were estimated using the approximate normality method and statistically tested with Fisher's exact probability test. All models were adjusted for age, sex, education, and TBI severity at baseline. Stratified analyses were performed to explore the efficacy of the L-oxiracetam intervention on cognitive function in patients with different age (< 60 vs. 60 + years), sex (male vs. female), education (none vs. Primary vs. Secondary school or Higher), and TBI severity (mild vs. moderate). Moreover, multiplicative interactions were tested by including a cross-product item in the model for the intervention group with age, sex, education, or TBI severity.

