**2 Trial Objectives**

- Primary objectives
- To evaluate the efficacy of L-oxiracetam on functional outcome in patients with TBI.
- To evaluate the safety of L-oxiracetam in patients with TBI.
- Secondary objectives
- To analyse changes in function and disease severity of patients with TBI treated with either L-oxiracetam, oxiracetam or placebo.
- Exploratory objectives
- To evaluate influence in subgroup (such as age, gender and so on) in patients with TBI treated with either L-oxiracetam, oxiracetam or placebo.

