7.1.2 Secondary endpoints

The secondary outcome measures include:

- Changes in scores on the LOTCA and GCS at the end of treatment compared to baseline;
- Changes in scores on the MMSE and MoCA at the end of treatment and 90 days post-treatment compared to baseline;
- The percentage of subjects at each level of the GOS-E at the end of treatment and 90 days post-treatment;
- ADL-BI at the end of treatment, 30 days, 60 days, and 90 days.

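### The blanket p ≤ 0.05 rule in Section 14 lets any of the 12 secondary outcomes be declared significant, unadjusted and even if the primary LOTCA comparison fails

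*Protocol*

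**What the plan says.** Section 14 of the protocol fixes the level and the decision rule in two sentences: "All hypothesis tests were two-sided with α = 0.05. A P-value ≤ 0.05 indicated statistical significance". The Statistical Analyses entry of the Synopsis repeats both. Neither place separates primary from secondary tests.

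Section 7.1.2 lists the secondary outcomes:

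- "Changes in scores on the LOTCA and GCS at the end of treatment compared to baseline" (2 outcomes)
- "Changes in scores on the MMSE and MoCA at the end of treatment and 90 days post-treatment compared to baseline" (4 outcomes)
- "The percentage of subjects at each level of the GOS-E at the end of treatment and 90 days post-treatment" (2 outcomes, if each visit is one test)
- "ADL-BI at the end of treatment, 30 days, 60 days, and 90 days" (4 outcomes)

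For the primary outcome, Section 14 names two contrasts: L-oxiracetam against oxiracetam and against placebo. The secondary continuous outcomes get mean differences with 95% CIs from ANCOVA, and GOS-E gets rate differences and Fisher's exact test. Section 2 attaches the exploratory label only to the subgroup objective: "To evaluate influence in subgroup (such as age, gender and so on) in patients with TBI treated with either L-oxiracetam, oxiracetam or placebo".

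**The concern.** A rule covering all hypothesis tests covers the secondary ones. The protocol marks lower-status analyses elsewhere: subgroups are exploratory in Section 2, and the stratified analyses in Section 14 are described as exploring. The secondary endpoints get no such mark, and nothing makes their testing depend on the LOTCA result at 90 days.

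Followed literally, the plan allows a single MMSE, MoCA, GOS-E or Barthel result with p ≤ 0.05 to be reported as statistically significant in a phase 3 trial of an unmarketed drug, whatever happened to the primary endpoint. Several overlapping scales are measured at up to four times, so an isolated significant result by chance is far more likely than the per-test 5% suggests.

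**Working it through.** **1. The level the plan uses.** Section 10 gives means of 26.0 and 22.8 (difference 3.2), SD 11.0, α 0.05 and power 0.8. With two-sided 0.05:

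n per group = 2 × (11.0/3.2)² × (1.960 + 0.842)² ≈ 185.5, rounded up to 186.

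The protocol states 190, which is within 3%. A one-sided test would need 147 per group, and α = 0.025 would need 225. The plan therefore works with a two-sided 0.05 that is not split between comparisons, as Section 14 says. The protocol states no family-wise rate for the secondaries, so there is no figure of its own to reproduce there.

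**2. Number of tests.** From Section 7.1.2: LOTCA 1 + GCS 1 + MMSE 2 + MoCA 2 + GOS-E 2 + ADL-BI 4 = 12 outcomes. If the two contrasts named for the primary also apply to the secondaries, 12 × 2 = 24 tests. This counts GOS-E once per visit; testing each of its eight levels would give (10 + 16) × 2 = 52.

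**3. Independent tests as an upper reference.** P(at least one) = 1 − 0.95^m. For m = 12 this is 46.0%; for m = 24 it is 70.8%. The expected number of p ≤ 0.05 among 24 true nulls is 24 × 0.05 = 1.2, whatever the correlation.

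**4. Correlated tests.** Inputs from Section 10: arms of 236, 236 and 118. The two contrasts share the L-oxiracetam arm. In units of σ²/236, their covariance is 1 and their variances are 2 and 3, so their correlation is 1/√6 = 0.41. The correlation between outcomes is not in the protocol. It is assumed equal for all pairs and varied. Each contrast is tested at |z| > 1.96 under true nulls in 200,000 or more simulated trials.

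| Assumed correlation | 24 tests, either direction | 24 tests, favouring L-oxiracetam | 12 placebo contrasts, either direction | 12 placebo contrasts, favouring L-oxiracetam |
|---|---|---|---|---|
| 0.3 | 62% | 34% | 40% | 20% |
| 0.5 | 52% | 27% | 32% | 16% |
| 0.8 | 32% | 16% | 19% | 9% |
| 0.9 | 24% | 12% | 13% | 7% |

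**5. Sensitivity to the correlation pattern.** With 0.7 within a scale over time and 0.2 to 0.5 between scales, the 24-test figures are 49% to 59% in either direction and 26% to 33% in favour of L-oxiracetam.

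For a single test, the corresponding rates are 5% in either direction and 2.5% in favour of L-oxiracetam. Every scenario above exceeds them.

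**The case against.** The strongest reply is that testing order and the status of secondary endpoints are commonly settled in a statistical analysis plan, which may exist and is not shown. Silence on those points would be no fault. But Section 14 is not silent. It states a significance rule for all tests, and a later plan that restricted the rule would have to depart from it.

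The protocol's own ranking also counts against reading too much into the rule. There is one primary endpoint, and the sample size rests on LOTCA alone. The secondary objective is only to analyse changes. The continuous secondaries are described through estimates and CIs, and only GOS-E is expressly said to be tested. This stands as mitigation: nothing in the protocol says that a secondary result can establish efficacy. It does not cancel the explicit rule.

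Three stronger readings are tempting, and the document supports none of them:

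- **A false secondary finding has a chance of about 50%.** That figure needs 24 tests and a correlation near 0.5. The second contrast is inferred for the secondaries, and the correlation is assumed.
- **The protocol promises 5% across the secondaries and misses it.** It states no such family-wise rate.
- **A spurious benefit is about as likely as not if L-oxiracetam does nothing.** The 52% also counts results that favour the comparator. The rate in favour of L-oxiracetam is 27% at correlation 0.5. The 24-test model further requires oxiracetam to be inert. If oxiracetam works and L-oxiracetam does not, false benefits come essentially from the placebo contrasts, at 7% to 20%.

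**Conclusion.** The point holds in a limited form. As written, the rule allows any of the 12 secondary outcomes to be declared significant at an unadjusted two-sided 0.05, with no dependence on the primary result.

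For 24 tests with all nulls true, the chance of at least one such declaration is about 24% to 62% in either direction and about 12% to 34% in favour of L-oxiracetam. For the placebo contrasts alone it is about 13% to 40% and 7% to 20%. These ranges rest on equal correlations of 0.9 to 0.3 between outcomes and one GOS-E test per visit; the 24-test figures also rest on carrying both primary contrasts over to the secondaries. The exact size depends on these assumptions. The conclusion that the chance is well above the single-test rate does not. The point is worth correcting but does not threaten the primary analysis.

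**What to change.** In Section 14 and the Synopsis, limit the p ≤ 0.05 significance rule to the primary comparison(s). Add that all secondary endpoints are supportive and are reported as estimates with 95% CIs and nominal p-values, without claims of significance.

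If the sponsor wants formal secondary claims, it should prespecify a short fixed sequence of its own choosing. Each sequence would be tested at two-sided 0.05 only after the primary comparison with the same comparator has succeeded, and would stop at the first non-significant result. Error control across both comparators then depends on the success rule set for the two primary contrasts, so the sequence must be written to fit that rule.

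The cost is one or two sentences in each place, with no extra patients or data. The downside is that an isolated secondary p-value can no longer be called significant.

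### The primary endpoint has two contrasts, each at two-sided 0.05, with no testing order or success rule; if either may carry the claim and all arms are equal, false superiority is 4.7% rather than 2.5%

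*Protocol*

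**What the plan says.** Protocol Section 7.1.1 defines one primary endpoint: "The primary outcome measure is the change in scores on the LOTCA at 90 days post-treatment compared to baseline". Section 14 analyses it by ANCOVA and reports two contrasts, since "the mean differences between groups (L-oxiracetam vs. oxiracetam/ Placebo) and 95% CIs were estimated". The same section sets the level for everything: "All hypothesis tests were two-sided with α = 0.05. A P-value ≤ 0.05 indicated statistical significance".

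Section 10 gives each contrast its own sample size calculation. For the comparison with oxiracetam, the pilot changes are 26.0 ± 11.8 for L-oxiracetam against 22.8 ± 10.0. The spread, level and power are then fixed in one sentence: "The combined standard deviation (SD) for both groups was 11.0, with α set at 0.05 and 1-β at 0.8". On these inputs the calculation arrives at 190 per arm. The comparison with placebo uses 26.0 ± 11.8 against 20.0 ± 11.4, SD 11.6, again with α 0.05 and 80% power, and arrives at 204 and 102. After a 15% increase the arms are 236, 236 and 118.

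The primary efficacy objective in Section 2 is "To evaluate the efficacy of L-oxiracetam on functional outcome in patients with TBI". It names no comparator. The synopsis repeats these statements. Nowhere does the protocol rank the two contrasts, fix their order, share alpha between them, or say whether one or both must be significant.

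**The concern.** The two contrasts support different claims: efficacy over placebo, and superiority over a marketed active drug. With both at the full 0.05 and no success rule, the text does not say what a split result means, that is, one contrast significant and the other not. A split is a realistic outcome on the sponsor's own assumptions, as shown in the working.

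Two things are at stake. If either contrast may count as a positive primary result, the error over the pair exceeds the level of each test. And unless a rule is on record before unblinding, the reading of a split result could be settled with the data in view.

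**Working it through.** **Inputs.** Two-sided α 0.05 for each test (Section 14); differences 26.0 − 22.8 = 3.2 and 26.0 − 20.0 = 6.0, SDs 11.0 and 11.6, power 80%, arms 236/236/118 (Section 10); ratio 2:2:1 (Section 3.1).

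**1. The plan's own figure.** For the oxiracetam contrast, n per group = 2(1.960 + 0.842)² × 11.0² / 3.2² = 186 (187 with the noncentral t). The stated 190 agrees within 3%. At α 0.025 the formula gives 2(2.241 + 0.842)² × 11.0² / 3.2² = 225. So 190 fits an unsplit 0.05 and not a Bonferroni half. The placebo figure cannot be used the same way: its stated inputs give 90 and 45, not 204 and 102. That is a separate matter and does not affect the error rates below, which depend on the allocation only.

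**2. Correlation of the two tests.** They share the L-oxiracetam arm:

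ρ = (1/236) / √[(1/236 + 1/236)(1/236 + 1/118)] = 1/√6 = 0.408.

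**3. Error over the pair, all three arms equal, either contrast sufficient** (bivariate normal with ρ = 0.408, cut-off 1.96):

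| Event | Pair | Single test |
|---|---|---|
| At least one significant result favouring L-oxiracetam | 4.7% | 2.5% |
| At least one significant result in either direction | 9.3% | 5% |
| Both significant, any direction | 0.7% | – |

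The last row follows from 5% + 5% − 9.3%. A simulation of 2 million trials gave 4.6% and 9.3% for the first two rows. Independent tests would give 9.75% in the second row.

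**4. Error when oxiracetam differs from placebo.** L-oxiracetam cannot then equal both. At most one null hypothesis is true, so the chance of a false rejection is at most 5% two-sided even under an either-contrast rule.

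**5. Power under the planning assumptions.** The standardised differences at 236/236/118 are 3.2 / [11.0 √(2/236)] = 3.16 and 6.0 / [11.6 √(1/236 + 1/118)] = 4.59. The second line of the table assumes 200/200/100 evaluable patients, roughly 15% fewer (236 × 0.85 = 200.6); the protocol does not state that number.

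| Arms | vs oxiracetam | vs placebo | Both |
|---|---|---|---|
| 236/236/118 | 88.5% | 99.6% | 88.3% |
| 200/200/100 (assumed) | 82.9% | 98.8% | 82.3% |

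A win over placebo without a win over oxiracetam therefore has probability 99.6 − 88.3 = 11.3%, or 98.8 − 82.3 = 16.5%. This is the split that the protocol leaves without a reading.

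**The case against.** The strongest reply is that no error has been shown. The 0.05 in Section 14 is a level for each test; the protocol never promises 5% over the pair. A reader might infer that the protocol states a 5% overall error and actually runs at about 9%. The documents do not support that.

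Nor do they say that either contrast alone suffices. If both must be significant, or the order is fixed, each test is correctly run and sized at the full 0.05, and Section 10 would read exactly as it does. The fit of 190 to α 0.05 rules out a planned Bonferroni split for the oxiracetam contrast, and nothing more.

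The 9.3% also needs care. About half of it is false results against L-oxiracetam, which nobody would present as a success. It further requires all three arms to be equal, while Section 1.2 describes oxiracetam as an effective drug. Finally, a separate SAP could fix the order without contradicting the protocol, so it cannot be concluded that the success criterion will be chosen after the results are known.

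All of this stands, and it limits the size and certainty of the point. It does not remove it. Section 14 is itself headed as the statistical analysis plan, sets 0.05 for every test, and refers to no later document for the order. Whether one or both comparisons must succeed is part of the design of a confirmatory trial, and the text adopts neither of the readings that would hold the error at 5%.

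**Conclusion.** The point holds as an undefined success rule for two primary contrasts. The inflation is conditional: 4.7% instead of 2.5% for false superiority (9.3% instead of 5% in both directions) if either contrast may carry a primary claim and the three arms are truly equal. It is at most 5% two-sided if oxiracetam truly differs from placebo, if both contrasts are required, or if the order is fixed. The error figures rest on normal test statistics, equal variances and 2:2:1 allocation.

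This should be settled before unblinding, but it ranks below a must-fix. Confidence is moderate, because a SAP that is not at hand may already contain the rule.

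**What to change.** State one rule in Sections 2, 10 and 14 before unblinding, or point there to the SAP section that contains it. The preferred wording is: L-oxiracetam is compared with placebo first at two-sided 0.05; only if that result is significant in favour of L-oxiracetam is it compared with oxiracetam, also at two-sided 0.05. If the intention is that both contrasts must be significant for success, saying so is an equally valid solution. Report both estimates with their 95% CIs whatever the outcome.

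Either rule holds the overall error at 0.05 and needs no more patients. Under the planning assumptions the fixed order costs 0.2 points of power for the oxiracetam claim at 236/236/118 (88.3% against 88.5%), or 0.6 points at the assumed 200/200/100 (82.3% against 82.9%). Its one drawback is that superiority to oxiracetam cannot be claimed if the placebo test fails, which has a probability of about 0.4% (100 − 99.6) to 1.2% (100 − 98.8). A Bonferroni split is less attractive: power against oxiracetam falls to 82.1% at 236 per arm and about 75% at 200.
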